## Abstract

**Background:** Virtual reality (VR) has emerged as a promising treatment approach in rehabilitation for patients with multiple sclerosis (MS) due to its potential to increase patient motivation and rehabilitation adherence. One of the key features for rehabilitation adherence is patient satisfaction with the VR rehabilitation (VRR) program, and information on user satisfaction and not only effectiveness is required to systematically include VRR in routine clinical practice. Given that information on patient satisfaction with VRR is scarce, the primary objective of this study is to assess long-term patient satisfaction with a novel VRR program. This program has been specifically designed for MS patients by a multidisciplinary team of specialists, based on an effective conventional rehabilitation (CR) program. Secondarily, discomfort with VRR will be evaluated, and therapy adherence and changes in a variety of domains typically affected by MS will be compared between patients receiving VRR and patients receiving CR.

**Methods:** In this prospective single-center 6-months follow-up study, 32 and 16 MS patients will receive VRR or CR, respectively. Patients will attend twice weekly rehabilitation sessions on site during 4 weeks, and they will continue with rehabilitation at home for five additional months. Satisfaction, assessed by the User Satisfaction Evaluation Questionnaire (USEQ), at 6 months of the VRR program initiation will be the primary outcome. Secondary outcomes include adherence, disability, spasms and spasticity, balance, fatigue, activities of daily living (ADLs), depression, anxiety, work status, cognition, demographic, and clinical characteristics (in the VRR and CR groups), and discomfort (in the VRR group). Outcome measures will be assessed at baseline, and at 1 and 6 months of rehabilitation initiation.

**Discussion:** The study is intended to provide a better understanding of long-term patient satisfaction with a VRR program specifically designed for MS patients. Additionally, the study will provide information on long-term adherence, changes in motor symptoms, cognitive functions and patient-reported outcomes after the rehabilitation program. The results from this study will help to gather valuable knowledge on the use of rehabilitation with a new VR tool in MS patients.

## Introduction

Multiple sclerosis (MS) is the most frequent cause of non-traumatic neurological disability in young adults in developed countries. Its prevalence has substantially increased in the last three decades and it affects ~2.3 million people worldwide (1, 2). The disease is associated with a high economic burden for society, and Spain is the European country with the highest total annual cost per patient (3, 4).

The clinical presentation of MS is heterogeneous and depends on the location of demyelinating lesions within the central nervous system. The most frequent symptoms and signs observed at disease onset originate from the optic nerve, the brainstem or cerebellum, the spinal cord, and the cerebral hemispheres (5). Motor manifestations (such as spasticity, gait, and balance impairments), optic neuritis, and sensory symptoms appear early in the disease course (6), and usually lead to progressive limitation of daily life activities. The majority of patients at the initial phase of MS have reversible episodes of neurological deficits (known as relapses) that usually last for days or weeks (relapsing-remitting MS; RRMS). Over time, in a proportion of patients, the development of permanent neurological deficits and the progression of clinical disability become prominent (secondary progressive MS; SPMS). A minority of patients have a progressive disease course from onset (primary progressive MS; PPMS). Most patients with MS, regardless of the initial disease course, will eventually require assistance to walk (7). It has been estimated that the average disease duration from diagnosis to use of a permanent walking aid is ~13 years (8). In fact, these motor problems have recently been identified by MS patients as the symptoms most undermining their health-related quality of life (HRQoL) (9).

Along with motor limitations, up to 65% of MS patients present impairments in a variety of cognitive domains within a year of diagnosis, processing speed being the most frequently affected domain in this time period (10). Deficits in memory, attention, executive functions, and visual perceptual functions are also prevalent in a considerable number of patients (11). The combination of all these impairments poses a threat to patients' daily life and is associated with work difficulties and negative outcomes (12, 13), including an early loss of productivity (14).

Despite continuous advances in MS management and the availability of increasingly effective disease-modifying therapies (DMTs), patients still have a high disability burden over long periods of time. This increased period of disease disability provides at the same time greater potential for rehabilitative therapies to reduce impairment through the strengthening of residual capacities and learning of new strategies. Rehabilitation consists of individualized and goal-oriented tasks aimed at improving functional independence. A review of reviews on rehabilitation in MS found strong evidence for the benefits of physical therapy on function and participation (15). Cognitive rehabilitation, on the other hand, has also shown improvements in cognitive abilities (16), although the evidence is not as conclusive as for motor rehabilitation.

In general, motor and cognitive rehabilitation therapy poses some significant challenges. On one hand, attending rehabilitation sessions on a regular basis might be difficult due to MS patient mobility difficulties, geographical location, and/or limited resources. On the other hand, traditional rehabilitation exercises are usually repetitive and tedious, which might decrease the patient's interest and could lead to reduced exercise adherence. Virtual reality rehabilitation (VRR) has been proposed as a promising therapeutic tool to overcome the drawbacks of conventional rehabilitation (CR).

Virtual reality rehabilitation offers the possibility of task-oriented and home-based training that allows the simulation of complex multisensory situations simulating everyday activities. The use of VR with lifelike scenarios in people with MS has shown to be safe and effective in motor rehabilitation, including gait, balance and arm mobility improvements (17–23). VRR not only engages patients in motor activities, but it simultaneously require patients to use cognitive abilities, since enriched virtual environments usually require greater attention and dual-tasking to complete the goal-oriented task (22).

Due to the stimulating and interactive nature of virtual environments in which rehabilitation exercises are presented as games, VRR has the potential to be a useful tool to increase motivation and therapy adherence (24). One of the key features for rehabilitation adherence is patient satisfaction with the program. In line with this, a study has recently shown that MS patient satisfaction with a telerehabilitation program was the only factor that significantly differentiated between low and high adherence groups, while other factors such as fatigue, disability, physical and psychological impact of the disease, sleep quality, and HRQoL, among others, were not different between the two groups (25). The study also demonstrated that patient satisfaction with the program was a predictive factor for high rehabilitation adherence (25).

Despite VRR programs having been shown to be feasible and accepted by MS patients (17, 19, 23, 24), the evidence on MS patient satisfaction with VRR programs is scarce (26). Satisfaction, together with effectiveness and efficiency in a quantified context of use, define the usability of a system or product (27). Several questionnaires have been designed to evaluate usability in computer systems (28), but as far as we know, only one questionnaire so far has been validated to address satisfaction of use in VRR programs: the User Satisfaction Evaluation Questionnaire (USEQ) (29).

Importantly, most of the studies evaluating VRR programs in MS have used technologies such as Nintendo Wii Balance Board System and Microsoft Kinect Sensor Xbox 360 (22, 24, 30–33), which were created for entertainment of the general population (exergames) and were not specifically designed for rehabilitation of impaired functions (serious games). Furthermore, the feasibility of VRR in MS has usually been assessed after a 6-weeks (18, 19, 26, 34) or 10-weeks program (24), which might not be enough time to confirm patient acceptance of VRR in the long term.

There is presently limited evidence on MS patient satisfaction with VRR programs using gamified exercises to target MS needs. A better understanding of long-term patient satisfaction with a VRR program specifically designed by a multidisciplinary panel of experts in MS and experts in gamification, immersive narrative and interactive engineering, would allow customization of the program to patient needs, which would likely increase rehabilitation adherence, and hence improve clinical outcomes.

The primary aim of this pilot study is to evaluate satisfaction with a VRR program in patients with MS at 6 months of program initiation.

Secondarily, we aim to: (i) describe adherence to a VRR and a CR program during 6 months; (ii) compare changes after 6 months of VRR or CR in a variety of domains typically affected by MS, including HRQoL, fatigue, activities of daily living (ADLs), work status, depression, anxiety, disability, spasms and spasticity, balance, and cognition; (iii) evaluate the presence of discomfort during the VRR program; (iv) explore clinical and demographic characteristics associated with patient satisfaction with the VRR program.

An exploratory data analysis of the secondary objectives described above will be performed at 1 month of rehabilitation program initiation.

## Methods

### Study Design

To test the study objectives, a prospective single-center 6-months follow-up study will be conducted in patients with MS. During this period, MS patients will be treated and/or evaluated by a multidisciplinary team of specialists including neurologists, physiotherapists, physiatrists, neuropsychologists and nurses. After patients have signed the informed consent form and have been confirmed to meet the selection criteria, they will be randomized 2:1 to the VRR group or the CR group. This unequal ratio has been used so that each subject entering the study has twice the probability of being assigned to the VRR group, which is expected to positively impact the patient experience with the rehabilitation program. In the VRR group, patients will receive 4 CR sessions plus 4 VRR sessions at the hospital during ~4 weeks. In the CR group, patients will receive 8 sessions of CR at the hospital during ~4 weeks. After the on-site rehabilitation, both groups will continue with rehabilitation at home for an additional 5 months. The VRR group will receive a VR headset and the CR group will receive instructions on CR techniques and a notebook with cognitive tasks. Figure 1 shows an overview of the study design.

**Figure 1 F1:**
[figure not shown]
Study design.

The randomization lists will be created using the EPIDAT statistical software developed by the *Servicio de Información sobre Saúde Pública de la Conseller*í*a de Sanidade e Servicios Sociais de la Xunta de Galicia* (Spain) and the *Special Program for Health Analysis* (SHA) of the Pan American Health Organization (PAHO). A permuted block design with a computer random number generator will be used. The neurologist, physiatrist, and neuropsychologist involved in the assessment of the patient will be blinded to randomization. The physiatrist, physiotherapist, nurse, and neurologist treating the patient will be aware of the randomization. Both randomization and blinding are not required to achieve the primary aim of the study. However, we decided to randomize the patients to prevent selection bias and allow comparisons between groups (secondary aims). Blinding was also considered to be appropriate in order to increase the objectivity of the neurologist and neuropsychologists involved in patient assessment.

The number of study visits will be up to 4. A screening visit (V_0_) where the patient will be invited to participate in the study after being informed of its characteristics, a baseline visit (V_1_) where training on the VRR or CR will be conducted, a post-rehabilitation on-site visit (V_2_), and a post-rehabilitation at-home visit or study competition visit (V_3_). All visits will be conducted at the time of routine clinical practice visits. The screening visit (V_0_) and baseline visit (V_1_) might be combined, and in that case the total number of study visits will be 3.

The study was approved by the Ethics Committee of the Hospital Universitario de la Princesa on 26/09/2019 and will be conducted in accordance with the ethical standards laid down in the 1964 Declaration of Helsinki.

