### Intervention

Patients will attend 8 on-site rehabilitation sessions during 4 weeks (2 sessions per week) of ~2 h duration each. The rehabilitation sessions will be conducted by a physiotherapist in groups of a maximum of 4 at the physiotherapy room of the Hospital Universitario de la Princesa in Madrid (Spain). Groups will be formed according to patients' functional level measured by the EDSS (36), resulting in three subgroups (low, medium, or high functional level) in each rehabilitation group (VRR and CR). The number of sessions conducted on site will provide sufficient training to allow patients to continue performing the rehabilitation exercises at home independently.

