### Conventional Rehabilitation

#### Physical Exercises

All patients will receive CR on site (eight sessions in the CR group and four sessions in the VRR group). The rationale for including four sessions of CR in the VRR group is to ensure that all patients become familiar with all the exercises and learn to perform the movements correctly before doing them within the virtual environment. Patient status and suitability to perform the exercises (heart rate, blood pressure, temperature, and fatigue) as well as the temperature and humidity of the room will be evaluated at the beginning of each session.

During the rehabilitation sessions, exercises will be based on a standardized rehabilitation program (37) which has been extensively described elsewhere. Briefly, to ensure appropriate muscle activation, a 30-min warm-up with light aerobic activity and mobilization using the cycle ergometer or pedal exerciser will be performed. This will be followed by stretching, and exercises aimed at improving spasticity (~10–15 min), coordination and balance (~10 min), mobilization (~10–15 min), breath control (~10–15 min), and gait (~10–15 min). The exercises will be conducted in supine, prone, quadruped, knees and standing positions, and they will be interspersed with rest periods. Energy-saving techniques will be also taught during the sessions.

All exercises will be individually tailored according to the patient's abilities and needs. Exercises are classified according to the level of difficulty (low, medium, high), and patients will be assigned to a group (low, medium, and high function) based on an initial evaluation. Given that all patients in the group will have a similar level of function, patients will easily adapt to the pace of the session. During all sessions, patients will be led and supervised by the physiotherapist, who will give personalized instructions on the exercises according to the patient's function and ensure all the exercises are performed safely. For the last session, patients will be engaged to attend accompanied by a family member in order to serve as a reinforcement for rehabilitation at home. Patients will be requested to perform the exercises at home in the presence of a family member and after having removed all possible obstacles in the play area to increase patient safety.

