During each on-site VRR session, the physiotherapists will supervise whether patients correctly perform all the exercises. The exercises have been classified in three categories according to their physical and cognitive difficulty (A, B, or C, corresponding to a low, medium and high level of difficulty). The level of difficulty and the type and number of physical exercises will be selected based on the functional status of each patient. The difficulty of the cognitive tasks will be automatically adjusted according to patient progress. Thus, a patient could simultaneously perform physical exercises of medium difficulty and cognitive tasks of high difficulty. The accuracy with which the patient performs the task will constitute the measure of game performance. Positive feedback will be provided by the system before, during, and after task performance to boost patient motivation. Patients will be encouraged to contact any member of the study team in case of discomfort, for any question regarding the study protocol, or in case of technical problems.

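### Functional level shapes the on-site programme, yet the stated VRR versus CR tests are unadjusted; with 32 versus 16 patients, baseline EDSS or functional level belongs in the comparison

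*Protocol article*

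**What the plan says.** **Allocation (Methods, Study Design).** Once eligibility is confirmed, "they will be randomized 2:1 to the VRR group or the CR group". On the method, "The randomization lists will be created using the EPIDAT statistical software" and "A permuted block design with a computer random number generator will be used". No stratification factor or block size is given. The same section says that randomisation is not needed for the primary aim and was added to prevent selection bias and to permit the between-group comparisons among the secondary aims.

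**Delivery.** Under Intervention, "The rehabilitation sessions will be conducted by a physiotherapist in groups of a maximum of 4". Groups are formed by EDSS, "resulting in three subgroups (low, medium, or high functional level) in each rehabilitation group (VRR and CR". Under Physical Exercises, "patients will be assigned to a group (low, medium, and high function) based on an initial evaluation". For the VRR sessions (Software), "The level of difficulty and the type and number of physical exercises will be selected based on the functional status of each patient".

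**Analysis (Statistical Analysis Plan section).** Mean 6-month changes are compared between arms by t-test, or by Mann-Whitney test where the distribution is not normal. No baseline covariate is mentioned. The primary analysis is descriptive: the USEQ total score in the VRR arm.

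**The concern.** Functional level is a measure of baseline disability, and it also determines which group a patient trains in and how hard the exercises are. It can be known at entry, since EDSS is an eligibility criterion, and EDSS is recorded again at baseline. Yet it appears neither in the stated allocation nor in the stated between-arm test.

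In a large trial this would matter little. With 16 patients in the smaller arm, the arms may differ visibly in their mix of low, medium and high function. If functional level predicts change in walking, balance, fatigue or cognition, part of an observed VRR versus CR difference could then reflect that mix, and the stated tests would not separate the two. What is at stake is the precision and readability of the secondary and exploratory comparisons.

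**Working it through.** **1. The plan's own sample size.** Inputs from Sample Size Calculations: SD 50, correlation 0.90, difference 20, two-sided alpha 0.05, power 0.80, ratio 2:1, drop-out 5%.
- SD of change = 50 × √(2 × (1 − 0.90)) = 22.36.
- CR patients = (1 + 1/2) × 22.36² × (1.960 + 0.842)² / 20² = 14.7, so 15 CR and 30 VRR.
- Dividing by 0.95 and rounding up gives 16 and 32.

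The stated figures reproduce, and nothing here disputes them.

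**2. Imbalance in one level, if the lists are not stratified.** Assume a level holds 16 of the 48 patients, and let X be the number of these in CR.
- Difference in share between arms = X/16 − (16 − X)/32 = (3X − 16)/32.
- A difference of at least 0.20 needs |3X − 16| ≥ 6.4, that is X ≤ 3 or X ≥ 8.
- X is hypergeometric (48 patients, 16 in the level, 16 in CR): P(X ≤ 3) = 0.116 and P(X ≥ 8) = 0.081, in total **0.196**.
- At least 25 points: 0.110. At least 30 points: 0.050.
- SD of the difference = 0.146.

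The level size matters. If the level holds 12 of 48, the 20-point probability is 0.073; if it holds 24 of 48, it is 0.125.

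**3. Imbalance in any of three levels (at least 20 points).**

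| Assumed level sizes | Probability |
|---|---|
| 16/16/16, fixed | 0.40 |
| One third each, membership random, blocks of 3 or 6 | 0.33-0.34 |
| 12/24/12, fixed | 0.21 |

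The first two rows differ only in whether level sizes are fixed or random. Block size makes no material difference without stratification.

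**4. Imbalance in mean level.** The SD of a standardised baseline difference is √(1/16 + 1/32) = 0.31. In simulation with random thirds, a difference of at least 0.5 SD in mean level occurred in about 11% of trials.

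**5. What that could do to one result.** The article does not say how change depends on functional level, so this step is illustrative. Score three equal levels 0, 1, 2: the SD is √(2/3) = 0.816, and 0.5 SD is 0.41 of a level. Suppose expected change differs between adjacent levels by 5, 10 or 20 points on the 0-100 scale. The shift in the arm difference is then 0.41 × 5 = 2, 0.41 × 10 = 4, or 0.41 × 20 = 8 points. The planned standard error is 22.36 × 0.306 = 6.8 points. The shift is therefore between small and about one standard error, and it vanishes if level does not predict change.

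**The case against.** **Stratification is not ruled out.** The article condenses a fuller protocol and speaks of randomisation lists in the plural. A reader might infer that allocation is definitely unstratified, but that would rest on silence. This stands, and so every probability above is conditional. It does not remove the point, because the unadjusted test is stated, and a stratified allocation would call for the same adjustment. The article defers further detail to a separate analysis plan, which may already contain it.

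**Chance imbalance is not bias.** Correct. Over repeated randomisations the comparison is unbiased and type I error holds. Analysing change from baseline already removes part of the effect of baseline status, though not all. Both arms tailor exercise to function, so a different exercise mix is the same disability imbalance seen again and should not be counted as a second fault.

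**Small CR groups.** A reader might infer that missing strata leave CR patients training nearly alone or waiting for a group to fill. The article sets only a maximum group size and reports neither situation. Sparse CR levels come mainly from spreading 16 patients over three levels. At 12/24/12 a perfect 2:1 split gives CR cells of 4/8/4. At 10/28/10 the chance that some CR level holds three or fewer patients is about 85% unstratified and 89% with stratified blocks of 3.

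**Changing allocation now.** Stratifying only the second half would lower the any-level figure for equal levels from 40% to about 15%. But half the patients are enrolled, totals would drift from 32/16, and small blocks are partly predictable in a single-centre trial whose treating staff know the allocation. The documents do not support calling for that change.

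**Conclusion.** The point holds as a minor one about the analysis. A baseline factor that governs group and exercise difficulty is absent from the stated between-arm tests. If the lists are unstratified, a 20-point imbalance has a probability of about 20% in a given level holding a third of patients, and about 33-40% in at least one of three equal levels. With 12/24/12 the latter falls to 21%. These figures rest on assumed level sizes.

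The consequence is possible loss of precision and a harder reading of any single secondary or exploratory result. The material does not support a claim that the VRR versus CR comparison is biased, or that it is weakened for every outcome: no effect on a particular outcome can be quantified from the article. The sample size and the primary USEQ estimate are untouched.

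**What to change.** Before the between-arm data are examined, prespecify the comparisons of 6-month change, and the exploratory 1-month change, as a linear model (ANCOVA) with terms for arm, the baseline value of the outcome, and baseline EDSS or functional level. Use a rank-based ANCOVA where the outcome is clearly non-normal. Report the adjusted arm difference with its 95% confidence interval.

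Baseline EDSS is the easier choice. It is already collected at the baseline visit by a neurologist unaware of allocation, and it needs no cut-offs, which the article does not give. When EDSS is itself the outcome, its baseline value serves both purposes.

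**Cost.** EDSS as a score uses one degree of freedom and a three-level factor uses two, plus one for the baseline value of the outcome. With all 48 patients analysed, residual degrees of freedom fall from 46 to 44 or 43. No new data are needed and the required sample size does not rise.

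Leave the allocation scheme as it is, and state in one sentence whether the lists are stratified by functional level. If they are, the model with functional level is the one that matches the design.
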